**Methods/Design:**

The ICON (Intensive Care Outcome Network) study is a multi-centre, longitudinal study of survivors of critical illness. Patients will be recruited prior to hospital discharge from 20–30 ICUs in the UK and will be assessed at 3, 6, and 12 months following ICU discharge for health-related quality of life as measured by the Short Form-36 (SF-36) and the EuroQoL (EQ-5D); anxiety and depression as measured by the Hospital Anxiety and Depression Scale (HADS); and post traumatic stress disorder (PTSD) symptoms as measured by the PTSD Civilian Checklist (PCL-C). Postal questionnaires will be used.

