**Discussion:**

The ICON study will create a valuable UK database detailing the prevalence of physical and psychological morbidity experienced by patients as they recover from critical illness. Knowledge of the prevalence of physical and psychological morbidity in ICU survivors is important because research to generate models of causality, prognosis and treatment effects is dependent on accurate determination of prevalence. The results will also inform economic modelling of the long-term burden of critical illness.

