### Aims and objectives of the study

The ICON study aims to:

Define the longer-term outcomes of a large, representative sample of survivors of adult, general ICU care in the UK quantitatively in terms of their survival, HRQoL and psychological morbidity 3, 6 and 12 months after ICU discharge.

Compare the mortality of survivors of adult, general ICU care with age-, sex- and condition-matched populations of people who have not experienced ICU care.

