### Procedure

Lists of patients meeting the study inclusion criteria will be sent from the participating hospitals to the trial office, which then submits this list to the Office of National Statistics (ONS). The ONS then performs two checks on the data. The first check cleans the list to maximise the identification of individual patients on the ONS databases; the second check identifies the patients that have died since hospital discharge. From the list of surviving patients generated by the ONS, contact with the patient's GP is made to act as a further check to confirm that the patient is still alive. Adopting this approach will hopefully prevent a questionnaire pack being mailed to a deceased patient and unnecessary distress being caused to their relative.

The three-month mailing pack consists of an introductory letter to the study, a patient information sheet, consent form, questionnaire set and a FREEPOST envelope. If the questionnaire pack is not returned, a reminder mailing is posted four weeks later. Once a patient is enrolled into the study, they will receive further study packs at 12 and 24 months post ICU discharge as long as they are not subsequently identified as deceased by the pre-mailing ONS check. The 12 and 24 month mailing packs comprise a reminder letter of the study, the relevant questionnaire packs and a FREEPOST envelope.

Again, if the patient has not returned either pack 4 weeks after the initial mailing, a second pack will be sent. If the questionnaire packs are not returned after the second mailing, no further attempts will be made to contact the patient.

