### Trial recruitment and baseline measurements

All patients discharged from all participating units will be given a generic discharge letter introducing the study to them and the possibility that they may receive a mailing from the ICON study team in the coming months. Data will be collected on patient demographics, ICU diagnosis, ICU stay, severity of illness using the Acute Physiology, and Chronic Health Evaluation (APACHE II) system [30] and APACHE II co-morbidity score.

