### Planned analyses

Using ICU admission as the event defining the start of follow-up, Kaplan-Meier curves will be constructed to illustrate survival. Age and sex matched control data will be requested from ONS in a 1:1 ratio with the patients in the study, and a control group Kaplan-Meier curve calculated from these data. A log-rank test will be used to determine the statistical significance of any differences noted.

It is almost certain that the ICU survivors will show a decreased longevity compared with the general population, so this initial testing will only be used to validate the study by showing similar results to previous investigations. However, as this is a non-randomised study, there are many potential sources for bias. To minimise the possibility that a difference in survival is due to confounders and not a real effect of the either illness or the ICU care, further covariate analysis will be undertaken. To determine the effects of covariates on survival, the Cox proportional hazards method will be used. The covariates included in the model will be age, sex, APACHE II predicted mortality, socio-economic status (from postcodes), geographical area (4 zones north to south based on hospital location), month of discharge, and 12 broad diagnostic categories based of the organ system involved in the acute illness. These results will be presented as a table showing the relative effects of ICU care and the covariates on survival.

The data on psychological illness (anxiety, depression and PTSD symptomatology), and quality of life will be largely descriptive and will be presented in tabular form.

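### The prevalence outcomes are committed only to descriptive tables of postal responders, which risks a non-response bias that a larger sample does not reduce

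*Protocol article*

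**What the plan says.** All places are in the protocol article.

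- **Purpose.** The abstract's Discussion says that "The ICON study will create a valuable UK database detailing the prevalence of physical and psychological morbidity", and that later research on causality, prognosis and treatment effects "is dependent on accurate determination of prevalence". Aims and objectives sets the target as "a large, representative sample of survivors of adult, general ICU care in the UK".
- **Data collection.** The abstract's Methods/Design states: "Postal questionnaires will be used". Under Procedure, the consent form travels in the same pack as the first questionnaires, a single reminder follows at four weeks, and then: "If the questionnaire packs are not returned after the second mailing, no further attempts will be made to contact the patient".
- **Size.** Sample size sets a minimum of 1000 survivors returning all questionnaires in the first year. It gives no response rate, prevalence or precision.
- **Baseline data.** Trial recruitment and baseline measurements says: "Data will be collected on patient demographics, ICU diagnosis, ICU stay, severity of illness", the last by APACHE II with its co-morbidity score. Data collection has ICUs submitting monthly patient lists with dates of birth and addresses, and ICNARC clinical data arriving quarterly. Data Handling describes linked databases.
- **Analysis.** Planned analyses acknowledges bias from the non-randomised design and answers it, for survival, with a Cox model and a named covariate list. Psychological outcomes and HRQoL get one sentence: they and "quality of life will be largely descriptive and will be presented in tabular form".

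**The concern.** The section that names a remedy for bias in the survival comparison names none for the prevalence outcomes, which are the study's main product.

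Selection is built into the design. A survivor who does not return the first pack is neither measured nor enrolled. Exclusion criteria also removes those unable or unwilling to consent, so first-wave non-returners could drop out of the denominator unnoticed. Avoidance is one of the symptom groups that the PCL-C measures, so return could plausibly depend on the outcome itself. At later waves, packs go only to enrolled patients not known to have died, so tables at successive waves may describe different people.

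At stake is whether the reported prevalence applies to ICU survivors or only to those who answer by post. Sampling error shrinks as responders accumulate. Bias from who responds does not, so the study's size gives no protection against it.

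**Working it through.** **No figure to reproduce.** The target of 1000 comes without inputs, so there is no stated precision or response rate to check. What follows is computed here.

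**Inputs**
- n = 1000 responders (Sample size).
- Prevalence p = 25%, assumed. It lies inside the ranges cited in Background: 12% to 43% for anxiety, 10% to 30% for depression, 5% to 64% for PTSD or its symptoms.
- Response proportion r: not in the article; assumed from 30% to 90%.
- Difference in prevalence between responders (pR) and non-responders (pNR): not in the article; assumed 10 points.

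**Step 1: sampling error.** Half-width = 1.96 × √(p(1 − p)/n) = 1.96 × √(0.25 × 0.75/1000) = 2.7 points. This treats patients as independent; clustering within ICUs is ignored.

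**Step 2: bias of the responder prevalence.** True prevalence = r·pR + (1 − r)·pNR, so bias = pR − true = (1 − r)(pR − pNR).

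| Response (assumed) | Bias for a 10-point difference | Bias ÷ 2.7 |
|---|---|---|
| 30% | 0.7 × 10 = 7.0 points | 2.6 |
| 50% | 0.5 × 10 = 5.0 points | 1.9 |
| 70% | 0.3 × 10 = 3.0 points | 1.1 |
| 90% | 0.1 × 10 = 1.0 point | 0.4 |

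The sign is open: responders may have more symptoms than non-responders, or fewer.

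**Step 3: difference needed for bias to equal the half-width**, 2.7/(1 − r): about 3.8 points at 30% response, 5.4 at 50% and 27 at 90%.

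**Step 4: a wider range of assumptions.** Take pR = 30% (half-width 2.8 points) and let pNR be 0.67 to 1.5 times that, so from 20.1% to 45%. The bias then runs:
- at 30% response: 0.7 × 9.9 = +6.9 to 0.7 × (−15) = −10.5 points;
- at 50%: +4.95 to −7.5;
- at 70%: +3.0 to −4.5;
- at 90%: +1.0 to −1.5.

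It is zero if the groups do not differ.

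**Step 5: a larger sample.** With 4000 responders at p = 25%, the half-width falls to 1.96 × √(0.1875/4000) = 1.3 points. At 50% response and a 10-point difference, the bias stays at 5.0.

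**Step 6: what weighting can do.** Assume two equal severity strata with prevalence 20% and 40%, so a true value of 30%.
- Response of 60% and 40%: unweighted prevalence = (0.6 × 20 + 0.4 × 40)/(0.6 + 0.4) = 28%.
- Response of 70% and 30%: (0.7 × 20 + 0.3 × 40)/(0.7 + 0.3) = 26%.

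Weighting each stratum by the inverse of its response returns 30% in both cases, but only if response is unrelated to symptoms within a stratum.

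**The case against.** The strongest objection is that this rests on silence in a condensed article. The sentence says largely descriptive; it does not say raw or unweighted. A response-weighted prevalence table is also descriptive and tabular, and a full protocol or SAP may deal with non-response. This stands in part. A reader might infer that the plan rules out correction, or that the estimates are already shown to be biased. The text supports neither: it shows a risk and no commitment to address it. What survives is that Planned analyses does state a bias strategy for survival and, beside it, commits the headline outcomes to tables alone.

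Four further inferences should be resisted.

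- **That the baseline data are collected to correct non-response.** The article does not say so; such variables have a stated analytic use only in the survival model. They could be used for this, subject to the Section 60 support that Data protection and PIAG approval says is still to be applied for.
- **That the bias would exceed the imprecision of the earlier single-centre studies.** Background gives those as 173 and 143 patients. At 25% prevalence their half-widths are 1.96 × √(0.1875/173) = 6.5 points and 1.96 × √(0.1875/143) = 7.1 points. A 5-point bias is smaller than both, and a 7-point bias falls between them. Nothing shows that those studies were free of the same bias.
- **That improvement over time would be only attrition.** The article specifies no analysis of change in these outcomes, and ONS checks identify deaths before each mailing. Mixing of recovery, drop-out and death is possible, not shown.
- **That weighting would cure the problem.** If symptoms themselves prevent return, weights built on severity and demographics leave that part of the bias in place. Scores from 3 months cannot help for people who never returned the first pack.

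**Conclusion.** The point holds as a risk that the plan should address, not as a demonstrated bias. The aim is accurate prevalence in a representative sample, the data come from self-selected postal responders, and the only stated analysis is largely descriptive tables.

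With an assumed 10-point difference, the bias exceeds the computed half-width once response falls below about 73% (1 − 2.7/10). At 90% response it is 1 point and of little consequence. Response rate, difference and direction are all assumptions. The change should be made because the risk falls on the main product and part of it can be reduced with data that the study plans to hold.

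**What to change.** In Planned analyses, state:

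1. A comparison of responders and non-responders at the first mailing on age, sex, diagnosis, ICU stay, APACHE II, co-morbidity and postcode-based deprivation, with the number mailed as the denominator.
2. Prevalence with inverse-probability-of-response weights from those variables, with 95% confidence intervals, beside the raw tables.
3. Later-wave estimates among those alive at that wave according to ONS, using the 3-month scores to handle drop-out.
4. A sensitivity range for symptom-dependent non-return, for example recalculating r·pR + (1 − r)·k·pR over a pre-stated range of k, the ratio of non-responder to responder prevalence.

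The cost is analysis wording and programming on data already due to be linked, and slightly wider intervals from weighting. One item lies outside the analysis: the Section 60 application must cover the use of non-responders' clinical data. As that application is still to be made, the decision should come first.

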### Economic issues

Utility analysis will be performed by estimating Quality Adjusted Life Years (QALYs) from the survival and EQ-5D data at 3, 12 and 24 months using standard techniques. A simple average of QALYs with measures of dispersion will be calculated. Assuming the data prove to be normally distributed, standard parametric testing will be used to compare the mean QALYs in ICU survivors with the age and sex matched controls held in other databases.

## Conclusion

The ICON study is a longitudinal study that seeks to provide rigorous data on the long-term outcome from ICU treatment in the UK, with a particular emphasis on psychological outcomes. Strengths of the study include comprehensive measurement of relevant outcomes and a relatively large projected sample size. Results from the ICON study should help inform policy and guide future research into the care and long-term outcomes of ICU patients.

## Abbreviations

CMP: Case Mix Programme; HADS: Hospital Anxiety and Depression Scale; HRQoL: Health-related Quality of Life; ICNARC: Intensive Care National Audit and Research Centre; ICU: Intensive Care Unit; NHS: National Health Service; ONS: Office of National Statistics; PCL-C: PTSD checklist (civilian); PTSD: Posttraumatic Stress Disorder; PIAG: Patient Information Advisory Group; QALYs: Quality-adjusted life years; SF-36: Short-form 36; UK: United Kingdom.
